### Perioperative management and monitoring

Upon arrival in the operating room, standard monitoring includes 5-lead electrocardiogram (ECG) and pulse oximeter. A peripheral venous cannula will be inserted, and patients will be sedated with midazolam intravenously. A radial arterial cannula will be inserted before anesthesia. Intravenous anesthesia is induced with midazolam (0.1–0.2 mg/kg), sufentanil (0.5–1 μg/kg), and rocuronium (0.6 mg/kg). The trachea will be intubated, and mechanical ventilation will start to achieve an end-tidal carbon dioxide tension of 35–45 mmHg, with limited inhaled oxygen concentration (FiO2) 0.4–0.6 and tidal volume (VT) 10 mL/kg during operation. After the induction, anesthesia will be maintained with continuous infusion of propofol 80–100 μg/kg/min or inhalation anesthesia 0.5–2 minimal alveolar concentration (MAC) combined with dexmedetomidine 0.5 μg/kg/h. Midazolam, sufentanil, and rocuronium will be given as needed. Arterial blood pressure, central venous pressure, and nasopharyngeal temperature will be recorded continuously. After systemic heparinization (3 mg/kg, activated clotting time > 480 s), the ascending aorta and superior and inferior lumen (or right atrium) will be cannulated. Standard CPB with a disposable hollow fiber membrane oxygenator (Affinity NT 541; Medtronic, USA) and a roller pump (Stockert-5, Sorin Group, Germany) will be started with a target output of 2.4~2.8 L/min m^2^ of body surface area. After aortic cross-clamping, cardio protection will be provided by cold-blood cardioplegia (1:4) at the dose of 20 mL/kg. The cardioplegia will be repeated half dose every 25 min during surgery. Surgery will be performed under mild hypothermia (33 °C), with MAP 50–70 mmHg and HCT 20–30% during CPB. After the cardiac surgical procedure, the heart will be defibrillated after aortic unclamping, if sinus rhythm does not resume spontaneously. After weaning from CPB, protamine will be used to reverse the effect of heparin. Patients will be transferred to ICU after surgery and extubated at the earliest clinically appropriate time when their ventilation, hemodynamics, and neurological status are considered stable by the attending physician.

### Safety management

The time, management strategies, and consequences of all adverse events will be recorded in the CRFs throughout the entire medical process. Intralipid is widely used in nutritional support for surgical patients and has been used in the clinic for more than 50 years. According to the instructions for the use of its drugs, there may be side effects such as allergic reactions, fever, dyspnea, and other toxic side effects, but the incidence is low. When the adverse reaction of intralipid occurs, the infusion of intralipid should be stopped immediately, patients will receive active, free treatment, and all costs will be covered by our project.

### Postoperative follow-up

Each patient will receive follow-up calls at 1 month, 6 months, and 1 year after surgery to answer questions regarding the presence and quality using the 15-item Quality of Recovery Questionnaire (QoR-15) [21, 22] and to provide the cardiac function data. Each patient will leave at least three phone numbers and receive a maximum of three telephone calls if contact could not be made.

### Data collection

All the related data are collected on the CRF. Preoperative data include general information about age, height, weight, and current and past medical history, especially heart disease history. The classification of the American Society of Anesthesiologists (ASA) was used to assess the risk within 24 h before surgery. Intraoperative data include the type and duration of surgery procedure, duration of CPB and aortic cross-clamp, method of anesthesia, and duration of anesthesia. Postoperative data include the morbidity and mortality; cardiac function evaluated by LVEF, LVEDS, and LVEDD; myocardial injury evaluated by CK-MB, cTnT, and BNP; short-term clinical outcomes during hospital stay (postoperative awakening time, mechanical ventilation time, ICU time, length of hospital stay); and total cost. The follow-up data include quality of life at three time points (1 month, 6 months, and 1 year), using the 15-item Quality of Recovery Questionnaire (QoR-15) and the echocardiography to evaluate the cardiac function.

### Data management and quality control

The original data will be recorded in the CRFs accordingly and maintained confidential. The study supervisor ([name]) will supervise the trial conduction every month, and there will not be a data monitoring committee (DMC). The data management and statistical analysis will be performed by the Center for evidence-based medicine and epidemiology, West China Hospital, Sichuan University. Because intralipid is a commonly used medicine in clinical anesthesia, and there have been no reports of serious adverse events, we will not perform an interim analysis.

## Statistical considerations

### Sample size estimate

PASS 15.0 software (NCSS Corp., Kaysville, UT, USA) is used to calculate the sample size. The sample selected for this trial was based on the results of a meta-analysis published by our research team, exploring the influences of inhalation anesthesia compared with total intravenous anesthesia on the patients’ outcomes after valve surgery [23]. The study included 13 randomized controlled trials (a total of 962 patients undergoing heart valve surgery) and found that the 30-day mortality rate was 5.3% and complex morbidity of major postoperative complications was 27%. Taking the complex morbidity of major complications in the meta-analysis as a control, the study has 80% power to detect a 30 relative risk reduction for the primary outcome of complex morbidity at a significance level (alpha) of 0.05 (two-sided), with an allowance of 10% of patients lost to follow-up or withdrawn from the study; finally, the calculated sample size of this study is about 1000 cases (500 cases each group).

### Data analysis

SPSS 22.0 software (IBM Co., Armonk, NY, USA) will be used to analyze the data. Baseline characteristics will be compared using chi-squared or Fisher’s exact tests. The continuous variables that have a normal distribution will be presented as the mean ± standard deviation (SD) or numbers (percentages) and compared using the *t* test or nonparametric test. The incidence of primary and secondary endpoints was measured using the chi-squared test or Fisher’s exact tests. A sensitivity analysis using the modified intention to treat (mITT) approach will also be performed. As a composite outcome, each individual outcome should be analyzed individually. Subgroup classification will be performed according to different types of surgery, Cox analysis will be used to analyze the mortality of different types of surgery, and multivariate logistic regression analysis will be used to correct for risk factors. Variables tested in the model will be selected if *P* < 0.10 or if they are clinically relevant. Results are considered statistically significant if *P* < 0.05. Two-sided significance tests will be used throughout.

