### Exclusion criteria

Patients who meet any of the following criteria will be excluded from participation:
Redo cardiac surgeryExperienced cardiogenic shock or cardiac arrest, left ventricular ejection fraction (LVEF) less than 30%, positive baseline serum cTnT or CK-MBAortic arch and other deep hypothermic circulatory arrest surgery, such as pulmonary thromboendarterectomyHeart transplantationUncontrolled hypertension (systolic pressure ≥ 180 mmHg or diastolic pressure ≥ 110 mmHg)Hyperlipidemia (TC ≥ 6.2 mmol/L or LDL-C ≥ 4.1 mmol/L)Significant hepatic (international normalized ratio > 2.0), pulmonary (forced expiratory volume-1 < 40% predicted, PaO2/FiO2 < 120) or renal disease (serum creatine level > 150 μmol/L)Severe coagulation dysfunction (Plt, PT, APTT, TT, FIB, and D-dimer were abnormal at the same time.)Any disorder associated with immunological dysfunction (e.g., malignancy or positive serological test for the HIV) in the last 6 monthsCurrent infections (meet at least two of the four SIRS diagnostic criteria: body temperature > 38 °C or < 36 °C, HR > 90/min, R > 20/min or PCO2 < 32.33 mmHg, WBC > 12 × 10^9^/L or < 4 × 10^9^/L or immature WBC > 10%)Pregnant womenPreoperative treatment with intralipid in the last 1 monthPreoperative treatment with nicorandil (an adenosine triphosphate-sensitive potassium channel opener) or sulfonylurea (an adenosine triphosphate-sensitive potassium channel blocker)Participating in other interventional studies

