### Study endpoints

The primary endpoints are complex morbidity of major complications during hospitalization (all systemic organ complications are graded as I–V in Table 1) and all-cause mortality within 30 days after surgery. Each individual outcome of the composite endpoint will be analyzed separately.

**Table 1 Tab1:** Grade of complication outcome of the subjects

Grade of complication outcome of the subjects	
I	Healed after temporary treatment
II	Lead to longer hospital stay
III	Life-threatening, but can be basically recovered during hospitalization
IV	Resulting in injuries for 30 days or longer after surgery, the quality of life is significantly reduced
V	Death within 30 days after the surgery (during the study period)

Note: The end of the operation until 24:00 on the day is 0 days after surgery, and the next day after surgery is 00:01–24:00 and so on

The secondary endpoints include (1) all-cause mortality 6 months and 1 year postoperatively; (2) the quality of life within 1 year after surgery, using the 15-item Quality of Recovery Questionnaire (QoR-15) [21, 22]; (3) the postoperative cardiac function evaluated by LVEF, LVEDS, and LVEDD at time points of 1 week, 1 month, 6 months, and 1 year postoperatively, and the myocardial injury evaluated by CK-MB, cTnT, and BNP at time points of 2 h and 24 h postoperatively; and (4) short-term clinical outcomes during hospitalization (postoperative awakening time, mechanical ventilation time, ICU time, length of hospital stay) and total cost are also detailed evaluated.

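### Postoperative LVEF is compared by unadjusted tests although baseline LVEF must be known for every patient: valid, but it gives up precision that costs almost nothing to recover

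*Protocol article*

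**What the plan says.** All references are to the protocol article.

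- **Cardiac function.** Study endpoints lists LVEF, LVEDS and LVEDD as secondary outcomes, measured "at time points of 1 week, 1 month, 6 months, and 1 year postoperatively". The Objective section makes better postoperative cardiac function one of the trial's aims.
- **Continuous outcomes.** Data analysis gives one rule: they are "compared using the *t* test or nonparametric test". No baseline covariate is named.
- **Baseline LVEF.** Exclusion criteria include "left ventricular ejection fraction (LVEF) less than 30%, positive baseline serum cTnT", so LVEF has to be known before a patient is enrolled.
- **Event endpoints.** "The incidence of primary and secondary endpoints was measured using the chi-squared test", with Fisher's exact test as the alternative. All-cause mortality at 6 months and 1 year is a secondary endpoint, so this sentence covers it.
- **Other models.** The only time-to-event method named is tied to subgroups: "Cox analysis will be used to analyze the mortality of different types of surgery". The only model named for adjusting for risk factors is logistic regression. Covariates are chosen as follows: "Variables tested in the model will be selected if *P* < 0.10 or if they are clinically relevant".
- **Loss.** Sample size estimate allows for 10% lost or withdrawn. Postoperative follow-up caps contact at three calls, with at least three telephone numbers held per patient.

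**The concern.** Patients differ in LVEF before surgery, and that difference carries through to follow-up. The trial admits LVEF from 30% upward and takes valve, coronary, aortic and combined procedures, so the baseline spread may be wide. A two-sample test on the postoperative value leaves all of that spread in the error term, while a model with baseline LVEF removes the part it predicts. The only adjusted model named for non-mortality outcomes is logistic regression, which is for binary outcomes and cannot do this for LVEF.

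What is at stake is precision on an outcome in the stated objective. The Background section itself puts the pilot's lack of a difference in LVEF and other short-term parameters down to small numbers.

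A smaller point concerns late mortality. A chi-squared test at 6 months or 1 year needs a known status for each patient it counts, and the overall comparison of arms has no stated method that uses the follow-up time of patients lost earlier.

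**Working it through.** **1. The plan's own figure.** Inputs from Sample size estimate: control rate 27%, relative reduction 30 (read as 30%, the percent sign being absent), two-sided alpha 0.05, 80% power, 10% loss.

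- Treated rate: 0.27 × 0.70 = 0.189.
- Two-proportion formula, pooled: 422 per arm; with continuity correction: 447 per arm.
- With 10% loss: 447 / 0.90 = 497 per arm, 994 in total.

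This agrees with the stated figure of about 1000. It concerns complex morbidity only, and nothing below changes it.

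**2. LVEF with and without baseline.** Inputs: 500 × 0.90 = 450 per arm; two-sided 0.05; 80% power. The correlation r between baseline and follow-up LVEF is an assumption, because the article gives none. The range used is 0.3 to 0.7.

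- Detectable difference, t test, in SD units: (1.960 + 0.842) × √(2/450) = 2.802 × 0.0667 = 0.187.
- With baseline adjustment the variance of the treatment difference is multiplied by 1 − r², so the detectable difference is 0.187 × √(1 − r²).
- Power for the effect that gives the t test 80%: Φ(2.802/√(1 − r²) − 1.960).

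| r (assumed) | 1 − r² | Variance cut | Sample-size equivalent, 1/(1 − r²) | Detectable difference (SD) | Power |
|---|---|---|---|---|---|
| 0 (t test) | 1 | none | 1 | 0.187 | 80% |
| 0.3 | 0.91 | 9% | 1.10 | 0.178 | 84% |
| 0.5 | 0.75 | 25% | 1.33 | 0.162 | 90% |
| 0.7 | 0.51 | 49% | 1.96 | 0.133 | 97.5% |

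**3. Late mortality.** This was simulated with 500 per arm, exponential times, 4000 runs, an assumed 1-year control risk of 5.3% to 10%, and non-informative loss of 0 or 10%.

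- Power of log-rank and chi-squared differed by at most 0.5 percentage points. At 8% risk and hazard ratio 0.5: 75.2% against 74.8% without loss, and 71.4% against 71.0% with 10% loss.
- Type I error stayed near 5% for both.
- Effect of 10% loss on a true 8% risk: the death hazard is −ln(0.92) = 0.0834 and the loss hazard −ln(0.90) = 0.1054. Observed deaths are 0.0834/0.1888 × (1 − 0.92 × 0.90) = 7.6% if the lost are counted alive. If they are dropped, the risk is 0.076/(0.076 + 0.828) = 8.4%. The shift is about 0.4 points either way.

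**The case against.** **For the plan.** Randomisation makes the unadjusted comparison of LVEF unbiased, the outcome is secondary, and the gain depends on a correlation the article does not state. At r = 0.3 it is only 4 points of power. All of this stands: the matter is efficiency, not error. It might also be said that the covariate rule lets baseline LVEF in as clinically relevant. That rule follows the logistic model, however, and does not reach continuous outcomes.

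**Is baseline available?** Data collection does not name LVEF among the preoperative data, and the schedule figure is not shown. For LVEF the exclusion criterion settles that it is known. For LVEDS and LVEDD nothing in the text shows a recorded preoperative value, so adjustment of those two is conditional.

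**Stronger readings that a reader might infer, and that the document does not support:**

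- *Twelve separate tests* (3 measures × 4 visits). The article gives a general rule and is silent on repeated measures, a detail that a separate analysis plan could hold.
- *Chi-squared wastes precision on mortality.* It does not to any material degree, as step 3 of the working shows. A comparison of proportions at a fixed time is a legitimate choice.
- *Patients lost are mishandled.* The article does not say whether they are dropped or counted alive. Bias between arms needs loss that differs by arm or is related to death, and Cox with censoring relies on a similar non-informative assumption.
- *Follow-up time is ignored altogether.* Cox is planned, though tied to types of surgery.
- *Unknown outcomes will outnumber deaths:* 10% of 1000 is 100, against 500 × (0.053 + 0.0371) = 45 deaths. The 10% is a sample-size allowance, not a forecast of unknown 1-year status. The 3.7% applies the morbidity reduction to mortality. The 45 are deaths by day 30, set against loss by 1 year.

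**Conclusion.** The point holds for LVEF, as a precision gain the plan leaves unused. The stated test is valid but less efficient than one that uses a value already needed for eligibility. The size is a 9% to 49% cut in variance, conditional on r between 0.3 and 0.7, 450 patients per arm with LVEF at the visit analysed, and a roughly linear relation between baseline and follow-up. The direction does not depend on the exact r: at this sample size any appreciable correlation favours adjustment.

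For late mortality only a minor addition is warranted. Its value is limited to letting patients with incomplete follow-up contribute the time they were observed. It should not be presented as correcting an invalid test.

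**What to change.** 1. **LVEF.** Replace the t or nonparametric comparison with ANCOVA at a named visit, or with one repeated-measures mixed model containing arm, visit, arm-by-visit and baseline LVEF. Name one visit as the main contrast.
2. **LVEDS and LVEDD.** Use the same model if preoperative echo values are recorded. The sponsor should confirm this, and confirm that baseline LVEF is entered on the CRF and not only checked at screening.
3. **Mortality at 6 months and 1 year (minor).** Report by arm in all randomised patients with Kaplan-Meier estimates and a log-rank or Cox comparison, censored at the date last known alive. Keep Cox by type of surgery as the subgroup analysis.

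The cost is a few sentences of analysis wording, agreed before unblinding. The software named in the plan can fit these models. Item 1 needs no new data. Item 2 depends on the confirmation above. Item 3 needs the date of death or last contact, which the planned Cox analysis already requires.

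### Each outcome inside the composite falls under the same P < 0.05 rule as the main result; the individual complications should be labelled descriptive support

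*Protocol article*

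**What the plan says.** The instruction appears twice in the protocol article. Under Study endpoints: "Each individual outcome of the composite endpoint will be analyzed separately". Under Data analysis: "As a composite outcome, each individual outcome should be analyzed individually".

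The content of the composite is given under Study endpoints. "The primary endpoints are complex morbidity of major complications during hospitalization", together with all-cause mortality within 30 days. A parenthesis adds that "all systemic organ complications are graded as I–V in Table 1". The individual complications are neither listed nor counted.

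For inference, Data analysis states: "The incidence of primary and secondary endpoints was measured using the chi-squared test or Fisher’s exact tests". It then sets one threshold: "Results are considered statistically significant if *P* < 0.05", and "Two-sided significance tests will be used throughout". The component analyses have no separate status.

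**The concern.** Looking at the parts of a composite separately is good practice, because it shows what drives the overall result. The weakness is that the article attaches a general significance rule to everything it analyses. By that rule, a component with P < 0.05 is a significant finding whatever the composite shows.

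Two misreadings become possible. After a null composite, one organ complication that crosses 0.05 by chance could be reported as a demonstrated benefit or harm. After a positive composite, components that do not cross 0.05 could be reported as unaffected by treatment. The article describes the trial as a foundation for a later multicentre study, so a chance finding on one complication could steer that study's endpoint.

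**Working it through.** **Inputs from the article.** Sample size estimate: control morbidity 27%, 30-day mortality 5.3%, a 30 relative risk reduction (read as 30%), 80% power, two-sided alpha 0.05, 10% loss, about 500 per group. Data analysis: threshold 0.05.

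**Assumptions not in the article.** The number of components (2, 5 or 10), their rates apart from mortality, and their correlation.

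**1. The article's own figure.** A 30% reduction takes 27% to 0.27 × 0.70 = 18.9%. The two-proportion formula gives 422 per arm, or 447 with continuity correction. Allowing for 10% loss, 447 / 0.90 = 497 per arm, 994 in total. The stated figure of about 1000 is reproduced, and it rests on morbidity alone.

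**2. False positives if treatment does nothing.** For k independent tests at 0.05, the chance of at least one P < 0.05 is 1 − 0.95^k. The third column assumes a correlation of 0.3 between every pair of test statistics (equicorrelated normal).

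| Components k | Independent | Correlation 0.3 |
|---|---|---|
| 2 | 9.8% | 9.5% |
| 5 | 22.6% | 21% |
| 10 | 40.1% | 35% |
| 13 | 48.7% | – |
| 14 | 51.2% | 44% |

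For two tests the chance cannot exceed 2 × 0.05 = 10% under any correlation. With independent tests, one half is passed only at k = 14.

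Simulated patient data were also tried, with a correlation of 0.3 in the underlying tendency to each complication. The results were 22% for five components and 42% for ten, close to the independent figures. A correlation of that kind is much weaker once it reaches the test statistics.

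**3. Rare components.** With 450 per arm, and Fisher's test used where expected counts are small, the actual size of one test is 2.7% at a 1% event rate and 0.7% at 0.5%. Ten independent components at 1% then give 1 − (1 − 0.0268)^10 = 24%, and ten at 0.5% give 7%.

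**4. Context: what a non-significant component can show.** Mortality falling from 5.3% to 0.053 × 0.70 = 3.71% has mean rate 4.505%. The power is Φ{[0.0159√n − 1.96√(2 × 0.04505 × 0.95495)] / √(0.053 × 0.947 + 0.0371 × 0.9629)}.

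- n = 450 per arm: Φ[(0.337 − 0.575) / 0.293] = Φ(−0.81) = 21%.
- n = 500 per arm: Φ[(0.356 − 0.575) / 0.293] = Φ(−0.75) = 23%.

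By the same formula, morbidity at 27% has 82% power (450 per arm) or 86% (500 per arm).

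**The case against.** **The instruction may be narrow.** It speaks of individual outcomes, not individual complications. Under Study endpoints it directly follows the sentence naming two outcomes, morbidity and 30-day mortality, and the sample size section gives rates for just those two. The parenthesis on organ complications says what is graded; it does not order a test per organ. This stands. The narrow reading is open, and it caps the false-positive chance at about 10%.

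**A false positive is not the expected result.** A reader might infer that a chance significant complication is likely. The figures do not support that: with independent tests it needs 14 or more components, and the article gives no such count. For five or ten the risk is inflated but below one half.

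**The test for components is not named.** Chi-squared and Fisher's tests are assigned to primary and secondary endpoints; applying them to components is an inference. This stands, but the P < 0.05 rule refers to results in general, so it reaches the components whichever test is used.

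**Low component power is no defect.** A reader might infer that the trial fails because it cannot detect component effects. The article claims power only for complex morbidity, and parts of a composite are naturally rarer than the whole. This stands in full; the power figures only show how a negative component should be read.

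**An unseen plan may settle it.** A full protocol or analysis plan may list the components and set their status, so the missing list is not held against the article. What remains is a rule the article does state, which covers the components as worded.

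**Conclusion.** The point holds in a limited form. The article requires separate analysis of each outcome of the composite and calls any result below two-sided 0.05 significant, without making the component results supportive of the composite.

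The size depends on the reading. With morbidity and mortality only, the chance of at least one false positive is at most about 10%. With organ complications it is about 21–23% for five and 35–40% for ten, the lower figure in each range being for test statistics correlated at 0.3 and the upper for independence. The counts of five and ten are assumptions, and very rare complications would bring the risk down.

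Conversely, a non-significant component is not evidence of no effect: a true 30% reduction in 5.3% mortality would be detected only 21–23% of the time. That is a caution for interpretation, not a fault in the sample size.

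**What to change.** In Study endpoints and in Data analysis, state that the individual complications within the composite will be reported by arm as counts, with risk differences and 95% confidence intervals, as descriptive support for the composite, and that the P < 0.05 rule does not apply to them.

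The change should go no further. Confining the 0.05 rule to a single endpoint would silently demote 30-day mortality, which the article names among the primary endpoints. Its status, and the rule for secondary endpoints, are left unchanged. The two-outcome figure of about 10% is therefore not altered by this fix.

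The cost is a change of wording, and the loss of any stand-alone significance claim for a single complication. No data collection or sample size is affected.

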### Interventions

Patients who meet the enrollment criteria will be randomized 1:1 to either the control or the intralipid postconditioning (ILPC) group.

Patients in the ILPC group will receive an intravenous infusion of 2 mL/kg of 20% intralipid (medium-chain and long-chain fat emulsion injection C6~C24, Pharmaceutical) less than 10 min before aortic cross-unclamping. Intralipid should be infused over 10 min in constant speed, and standard or usual care will be given to patients before and after the intervention. The dose of intralipid is chosen on the basis of the bolus dose when it is used in rescuing the cardiac arrest caused by local anesthetic toxicity [8–11]. Patients in the control group received an equivalent volume of normal saline 10 min before aortic cross-unclamping. There will be no special criteria for discontinuing or modifying allocated interventions.

Three investigators ([name], [name], and [name]) will explain the treatment intervention in detail and supervise the compliance of intervention throughout the entire procedure (from maintenance of anesthesia to transport to ICU).

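### The adjusted logistic model selects covariates from the data, does not exclude variables that end after the infusion, and has no stated endpoint or rank

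*Protocol article*

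**What the plan says.** All statements are in the protocol article.

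- Data analysis, on the endpoints: "The incidence of primary and secondary endpoints was measured using the chi-squared test or Fisher’s exact tests".
- Data analysis, later, in the sentence that also covers surgery-type subgroups and Cox analysis of mortality: "multivariate logistic regression analysis will be used to correct for risk factors". The next sentence gives the selection rule: "Variables tested in the model will be selected if *P* < 0.10 or if they are clinically relevant". No endpoint is attached to this model, no covariates are listed, and the test that produces the P value is not named.
- Data analysis, on the only analysis given a secondary status: "A sensitivity analysis using the modified intention to treat (mITT) approach will also be performed".
- Data collection: "Intraoperative data include the type and duration of surgery procedure, duration of CPB and aortic cross-clamp, method of anesthesia, and duration of anesthesia".
- Interventions: the infusion is given "less than 10 min before aortic cross-unclamping".
- Perioperative management and monitoring: any defibrillation, and then weaning from CPB, follow unclamping.
- Discussion (limitations): anesthetic doses will be tabulated by arm, and they are described there as baseline data.

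**The concern.** Three features of the adjusted model are fixed badly.

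First, the covariates depend on the data. If P < 0.10 means a screen against the outcome (the likely reading), the adjustment set is known only once outcomes are in. If it means the between-arm comparison of baseline characteristics, the set is known only once the arms have been compared. The clinical-relevance route has no list to constrain it.

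Second, nothing restricts candidates to variables known before the infusion. CPB, surgery and anesthesia duration are all collected, and all are completed after it. The trial's hypothesis is better cardiac function after reperfusion, so an effect on weaning and on CPB time is plausible. A variable that treatment improves and that predicts complications carries part of the treatment effect. Conditioning on it removes that part from the estimate.

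Third, the model has no stated endpoint and no stated rank. If the adjusted and unadjusted results disagree, the protocol does not say in words which one decides.

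**Working it through.** **1. The plan's own sample size.** Inputs from Sample size estimate: control rate 27%; a 30 relative reduction, read as 30%, so 0.27 × 0.70 = 18.9%; two-sided alpha 0.05; power 80%; 10% loss.

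n per arm = [1.960·√(2·p̄·(1−p̄)) + 0.8416·√(p1(1−p1) + p2(1−p2))]² / (p1−p2)², with p̄ = 0.2295:

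(1.960 × 0.5947 + 0.8416 × 0.5919)² / 0.081² = 2.768 / 0.006561 = 422.

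With continuity correction, n/4·[1 + √(1 + 4/(n·0.081))]² = 447. Then 447/0.90 = 497 per arm, total 994. This reproduces the stated figure of about 1000. Without the correction the result is 469 per arm, total 938. The trial is therefore sized on an unadjusted comparison of two proportions, and changing the adjusted model does not affect the sample size.

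**2. Which collected variables end after the infusion.**

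| Variable | Ends at | Relative to infusion |
|---|---|---|
| Aortic cross-clamp duration | unclamping | almost entirely before |
| CPB duration | weaning, after unclamping | ends after |
| Surgery duration | end of surgery | ends after |
| Anesthesia duration | end of anesthesia | ends after |
| Total anesthetic dose | end of anesthesia | partly after |

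**3. Size of the bias, by hand.** The planned effect is ln[(0.189/0.811)/(0.27/0.73)] = −0.462. The part removed by adjustment is approximately ln(odds ratio per SD) × (shift/SD). The inputs are assumptions: CPB SD 30 min and odds ratio 1.5 per SD.

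| Assumed shortening of CPB | Log odds removed | Share of 0.462 |
|---|---|---|
| 0 min | 0 | 0% |
| 5 min | 0.405 × 5/30 = 0.068 | 15% |
| 10 min | 0.405 × 10/30 = 0.135 | 29% |

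**4. Size of the bias, by simulation.** 900 evaluable patients; about 27% vs 19% in every row; 15 baseline candidates, of which 4 are prognostic (log odds 0.3 per SD), screened at P < 0.10. The post-infusion variable has log odds 0.6 per SD, which is stronger than in step 3. 1,200 runs per row. All strengths are assumed.

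| Treatment shift | Log OR, baseline covariates only | Power | Log OR with post-infusion variable added | Power |
|---|---|---|---|---|
| 0 SD | −0.48 | 82% | −0.51 | 84% |
| 0.2 SD | −0.50 | 84% | −0.40 | 64% |
| 0.4 SD | −0.49 | 83% | −0.27 | 36% |
| 0.6 SD | −0.49 | 83% | −0.15 | 16% |

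With no shift nothing is lost. With a shift, the loss follows coefficient × shift: 0.6 × 0.2 = 0.12, 0.6 × 0.4 = 0.24 and 0.6 × 0.6 = 0.36.

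**5. Type I error.** Same set-up under no effect, 3,000 runs, Monte Carlo standard error √(0.05 × 0.95/3000) = 0.4 points.

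| Prognostic log odds per SD | Unadjusted | P < 0.10-screened model | Better of the two |
|---|---|---|---|
| 0.3 | 5.2% | 5.5% | 6.7% |
| 0.5 | 5.1% | 4.7% | 7.0% |

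A separate simulation with 10 candidates, 4 of them prognostic, gave 5.8% for the better of the two with weaker covariates (model AUC 0.66) and 7.1% with stronger ones (AUC 0.73). In the stronger setting the screened model alone gave 5.2%. Screening true baseline variables is therefore close to harmless for type I error. The excess comes from being free to declare either result.

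**The case against.** The strongest reply is that the protocol ties only one test, chi-squared or Fisher, to the endpoints, and that the sample size matches that unadjusted comparison. The logistic model comes later, in the sentence on surgery types, so it reads as supportive. No passage names CPB time as a covariate: Data collection lists what is recorded, not what is adjusted for. The Discussion only says that anesthetic doses will be compared between arms. Attenuation toward the null in a supportive model would leave the chi-squared result untouched. A condensed article may also leave the covariate list and the ranking to an analysis plan that is not shown.

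Much of this stands. A reader might infer that there are two competing primary analyses, that covariates are certainly screened against the outcome, or that adjustment for CPB time is planned. The documents support none of these: the first goes against the natural reading, the source of the P value is unnamed, and post-infusion adjustment is allowed but not announced. Nor do they state a rule of declaring the better of two results, so the 6–7% is conditional. A reader might also blame P < 0.10 screening itself for inflated error, but the simulations do not show that for baseline variables.

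The appeal to an unseen analysis plan does not remove the point. The selection rule is not left open; it is written down, and an analysis plan that followed it would carry it over. A supportive estimate adjusted for something treatment changes would still mislead anyone reading it beside the primary result.

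**Conclusion.** The point holds in limited form. The protocol fixes a data-driven covariate rule for its adjusted logistic model, places no limit at the time of infusion, and does not state the model's endpoint or rank.

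The bias from a post-infusion covariate cannot be computed from the documents. It is zero if treatment does not shift the variable. It is toward the null if treatment improves a prognostic one, and in the worked examples it ranges from 15% of the log odds ratio to most of it. Those sizes rest wholly on assumed shifts and covariate strengths. The type I error of about 6–7% instead of 5% applies only if either result could be declared, again under assumed covariate strengths. With chi-squared or Fisher confirmed as primary, the primary test is unaffected and the problem is confined to the adjusted estimate.

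**What to change.** In Data analysis:

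1. Delete the P < 0.10 rule.
2. Fix the adjustment set in advance to a few variables known before randomisation: planned surgery type, age, ASA class and screening LVEF. The exclusion criteria require LVEF for eligibility, but Data collection names it only among postoperative data and lists surgery type as intraoperative. The text should therefore say that the planned procedure and the screening value are used.
3. Bar variables measured or completed after the infusion from any treatment-effect model, including CPB, surgery and anesthesia duration and total anesthetic dose. They can still be reported descriptively by arm.
4. State the logistic model's endpoint, and state that one analysis is primary and the other supportive. Chi-squared or Fisher may stay primary.

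The cost is analysis wording before unblinding; the sample size is unchanged. Two further changes are optional and not needed here. One is to make the adjusted model primary: in the 10-candidate simulation, fixed adjustment gave 85–87% power against 82–83% unadjusted, under assumed covariate strengths. The other is to drop significance tests from the baseline table.
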